## **1. Summary of the research plan**

### **1.1. Background and rationale**

In recent decades, the proportion of women medical students has increased worldwide and has now outmatched their representation in the general population. This contrasts with the underrepresentation of women in leadership positions. In Switzerland, only 12% of senior doctors heading a medical service in 2018 were women; only 18% of full or associate professors in Swiss Universities were women. There are various reasons for this gender imbalance, including difficulties managing academic career, relationships and family. Another reason has been gender discrimination against women as their careers progress, such as in the selection of future medical specialists, the offer of mentoring, or the awarding of grants. Gender imbalance has also been demonstrated in contributions to research; men are more frequently assigned tasks considered more prestigious, whereas women more frequently receive operational tasks. These differences explain why women are less often at the strategic last-author position and more frequently in a less valued position. While we have identified an apparent gender gap during the research process, to our knowledge, no one has yet explored the existence of gender bias at a later point in the pipeline: specifically, during the editorial decision-making process, once the results of the research have been submitted for publication. A potential gender bias at this level could also explain why women have lower h-indices and, as a result, are still underrepresented among professors in universities. Geographical bias can also be suspected during the editorial decision-making process as it was highlighted in one ancillary study to the Athena project, and it will be also investigated as a post-hoc assessment.

### **1.2. Overall objectives and specific aims**

Our primary objective is to study the association of first authors' gender with acceptance for publication of original research articles sent for peer review. Our secondary aims are also 1) to study the association of last authors' gender with acceptance for publication of original research articles sent for peer review; 2) to examine the existence of a geographical bias during the editorial decision-making process; 4) to assess the existence of an independent gender bias against first authors at key decision points (first and last decision by editors, peer reviewers' score and recommendations) in the editorial decision-making process from initial submission to final decision.

### **1.3. Methods**

This will be a case-control study nested in a retrospective cohort of original articles submitted to medical journals during an 8-year period. The primary outcome will be women's (or men's) rate of acceptance for publication after peer review. The main exposure variable will be the first author's gender. Corresponding and last authors' gender will also be assessed in secondary analyses. Other exposure factors will be year of publication and key variables related to the research described in the manuscripts, as well as editors' and reviewers' gender. We will also assess the geographical affiliation of the first and last authors, and of the editor as other exposure factors associated with the acceptance for publication. Finally, we will assess if diversity in the research team, defined by any differences in the countries and geographical affiliations of the first and the last authors is associated with the acceptance for publication. The handling editor's gender will be assessed as an effect modifier in the association between the first author's gender and acceptance for publication.

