#### 2.3.7.2. Exposure variables and other confounders

The main exposure factor of interest is **first-author gender**. Other exposure factors assessed are: corresponding and last-author gender, handling-editor gender.

We will also collect data on: year of submission, study design, sample size, statistical significance of main results, funding disclosure, first author’s country of affiliation (reflecting somehow the author’s ethnicity/race), number of authors on the byline, number of reviewers who peer reviewed the manuscript, number (proportion) of women among all reviewers, number (proportion) of reviewers with same region of affiliation as the first author, and first author’s degrees (MD, PhD). If available, we will extract the reasons for rejection mentioned in the journal decision letter.

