#### **2.3.9.2. Statistical analyses**

Statistical analyses will be done by the postdoctorate under the supervision of [name]. We will present descriptive statistics for the proportions of women first authors that were: rejected without external review; sent for external peer review; rejected, accepted or invited to revise a manuscript after external peer review; and rejected and accepted after revision. To take into account clustering at the journal level, we will perform mixed-effects logistic regression to model the influence of the first author's gender on the odds of acceptance for publication, after adjustment for the confounders and covariates (cf. appendix 7) and using the journal as a random effect. We will perform the same logistic regression model to answer our secondary objectives to study the influence of corresponding-author gender or last-author gender on the acceptance for publication. To test whether the handling editor's gender or reviewers' gender modifies the association between first-author gender and the acceptance rate, we will include an interaction term between these two predictors. We will also test interactions of first author gender, respectively with the scope of the journal and with time on a yearly scale. Journals will be anonymised, therefore separate journal effects will not be presented when we publish the results but we will provide journal level data to individual journals upon request.

In the retrospective cohort, we will describe and compare, using Chi-2 tests, the proportion of women first authors for articles at the following points in the decision-making process: rejection without review; sent for peer review; rejected, accepted and sent for revision after peer review; and between articles rejected at any stage versus articles accepted for publication. To test whether the reasons for rejection mentioned in decision letters varies between men and women first (then corresponding and last) authors, we will include an interaction term between these two predictors in a mixed-effects logistic regression model with rejection as the dependent variable and journal as the random factor. All analyses will be performed using STATA 17.0 IC (StataCorp LP, College Station, TX, USA) and R software (version 4.0.5).

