## THE ATHENA STUDY: FIRST AUTHOR'S GENDER AND ACCEPTANCE FOR PUBLICATION

**Appendix 7.** Data extracted for the case-control study.

| Variables                                                  | Description                                                                                                                                                                                                                                          |
|------------------------------------------------------------|------------------------------------------------------------------------------------------------------------------------------------------------------------------------------------------------------------------------------------------------------|
| Unique ID of manuscript                                    | tracking number generated during submission process                                                                                                                                                                                                  |
| Journal identifier                                         | ##                                                                                                                                                                                                                                                   |
| Scope of the journal                                       | 1= infectious diseases journal 2= family medicine 3=internal medicine
4=others                                                                                                                                                                    |
| Date of submission                                         | __ / __ / ____                                                                                                                                                                                                                                       |
| Handling editor's gender                                   | 0=man, 1=woman                                                                                                                                                                                                                                       |

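### The editor's geographical affiliation is planned only as an exposure for acceptance; without an author–editor region match, same-region favouritism cannot be separated from other effects

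*Protocol*

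**What the plan says.** Protocol section 1.2 lists as a secondary aim "to examine the existence of a geographical bias during the editorial decision-making process". Section 1.3 gives the variables for it: "We will also assess the geographical affiliation of the first and last authors, and of the editor as other exposure factors". It adds a measure of diversity in the author team, "defined by any differences in the countries and geographical affiliations of the first and the last authors".

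The same protocol relates decision-makers to authors in two other places:

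- **Editor gender (1.3):** "The handling editor's gender will be assessed as an effect modifier in the association between the first author's gender and acceptance for publication". Section 2.3.9.2 gives the interaction term for it.
- **Reviewer geography (2.3.7.2, repeated in Appendix 7):** "number (proportion) of reviewers with same region of affiliation as the first author".

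No section matches the editor's region to the author's. The further interactions in section 2.3.9.2 are not geographical: "We will also test interactions of first author gender, respectively with the scope of the journal and with time on a yearly scale". In Appendix 7 the only editor characteristic is "Handling editor's gender". The editor's affiliation is also missing from section 2.3.7.2 and from Appendix 8.

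**The concern.** A main effect of editor region compares acceptance between editors of different regions, averaged over the authors they handle. That is leniency or strictness. Geographical bias by an editor means that the same editor's decision depends on where the author works, which is a statement about the author–editor pair.

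If only main effects are fitted, the editor coefficient can sit near 1 under marked same-region favouritism, and can be clearly different from 1 when no author is treated differently by region. Some or all of the favouritism then appears in the author-region coefficient, where it cannot be told apart from a disadvantage that all editors apply alike. The distinction has practical weight, because section 1.4 links the findings to remedies aimed at editors, such as anonymising authors' names.

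**Working it through.** **Plan's own figures.** The protocol states no effect size, region split or sample size for any geographical analysis, so there is no figure to reproduce. From section 2.3.8, 172 journal-years × 20 = 3440 cases, with as many controls. Everything else below is an assumption.

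**Assumed inputs.** There are two regions. A share f_E = 0.70 of editors and a share f_A = 0.50 to 0.60 of first authors come from region A. Editors are allocated independently of author region. Acceptance in different-region pairs ranges from 20% to 50%, and articles are then rebalanced to 3440 accepted and 3440 rejected. There is no journal effect and there are no covariates.

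**Algebra.** Let a and e be 1 if the author or editor is from region A, and 0 otherwise. The same-region indicator is

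s = a·e + (1 − a)(1 − e) = 1 − a − e + 2ae.

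Suppose the only true effect is favouritism, log-odds = constant + ln(θ)·s. With a and e independent, the best main-effects approximation has

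- editor coefficient ≈ (2f_A − 1)·ln θ
- author coefficient ≈ (2f_E − 1)·ln θ.

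The editor coefficient therefore depends on the author mix, and the author coefficient on the editor mix.

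**Scenario 1: favouritism θ = 1.5, no other effect** (ln 1.5 = 0.405)

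- Editor, f_A = 0.50: 0 × 0.405 = 0, OR 1.00.
- Editor, f_A = 0.60: 0.20 × 0.405 = 0.081, OR 1.08.
- Author, f_E = 0.70: 0.40 × 0.405 = 0.162, OR 1.18.

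Logistic regression on the expected counts over the acceptance range agrees:

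| Model | Editor-region OR | Author-region OR | Same-region OR |
|---|---|---|---|
| Main effects only | 0.99-1.09 (p 0.98 to 0.12) | 1.17-1.18 (p about 0.001) | not fitted |
| With same-region term | 1.00 | 1.00 | 1.50 |

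**Scenario 2: editor strictness OR 1.4, no dependence on author region.** Main effects give an editor OR of 1.40 (p < 0.0001). When the same-region term is added, it is 1.00.

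**Sensitivity: favouritism θ = 1.3** (ln 1.3 = 0.262). The main-effects editor OR is 1.00, 1.05, 1.11 and 1.17 as f_A goes through 0.5, 0.6, 0.7 and 0.8. For example, at 0.8, 0.60 × 0.262 = 0.157, OR 1.17. The same-region term returns 1.30 throughout. With a true strictness OR of 0.80 added, the editor OR moves from 0.80 at f_A = 0.5 to 0.94 at f_A = 0.8, so strictness and favouritism are mixed. The extended model recovers 0.80 and 1.30.

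**The case against.** **No model is fixed.** Section 1.3 is a summary, and section 2.3.9.2 gives no geographical model. Nothing says that interactions are excluded or that the editor coefficient will be read as bias. Editor gender is also listed among the exposure factors and is still made an effect modifier, so the label alone does not rule out a second role. A SAP that is not shown may add the term. This stands as a limit: the point is an omission in the role given to the variable, not a false statement. It remains that the protocol names the modifier role for editor gender and only the exposure role for editor geography.

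**The aim does not mention same-region favouritism.** It asks whether geographical bias exists, and author affiliation addresses that directly. A reader might infer from scenario 1 that the author-region OR of 1.17 is spurious, or that the aim fails as a whole. Neither follows. If most editors come from region A and favour its authors, those authors do have better average odds of acceptance, and the author term detects this correctly. Only the editor-related component stays unresolved.

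**The inputs are invented.** They are. The calculation also leaves out the journal random effect specified in section 2.3.9.2, in which editor region may be confounded with journal, and the 20% of missing values allowed for in section 2.3.9.1. The p-values are therefore optimistic. The algebraic relation between the coefficients does not depend on the sample size.

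**The stakes are low.** Section 1.1 says of geographical bias that "it will be also investigated as a post-hoc assessment", and section 2.3.3 does not list it among the secondary objectives. This is also right, and it limits how much weight the point deserves.

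**Conclusion.** The point holds as a specific, inexpensive improvement. The one role given to the editor's affiliation measures how readily editors from a region accept papers in general, and cannot isolate whether they favour authors from their own region. Under the assumptions above, favouritism of OR 1.5 leaves the editor OR between 0.99 and 1.09, while strictness of OR 1.4 with no bias gives 1.40. These sizes are illustrative and would change with the real region shares, the allocation of editors and the journal effect.

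The protocol does not support the stronger conclusion that its geographical analysis is invalid. The first- and last-author terms can still show an average disadvantage by region, so the aim is partly answered. The primary objective, its sample size and its model are not affected.

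**What to change.** 1. In sections 1.3 and 2.3.9.2, add an indicator that the handling editor and the first author share a region, or the author-region by editor-region interaction. Fit it beside both main effects in the mixed-effects logistic model with journal as random effect.
2. State that any conclusion on editor-related geographical bias rests on that term, and that the editor main effect describes general leniency or strictness.
3. Add the editor's affiliation to section 2.3.7.2 and Appendix 7, with the region grouping to be used.

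The cost is one data item, which section 1.3 already requires, one derived variable and one more secondary estimate. That estimate may be imprecise if editor region varies little within journals.

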### **1.4. Expected results and their impact**

If we observe that the likelihood of acceptance is at least 0.85 (odds ratio) for women compared to men first authors, it will contribute to our understanding of why women have lower publication rates and thus make slower

progress in academia. Thereafter interventions, such as editor anonymising regarding the author's name, could be assessed. Other methods are already implemented in some journals, such as fully open peer review journals where authors and reviewers are named, and this might impact on results as well. If we do not find gender bias in editors' and reviewers' decision-making, we will be able to conclude that the imbalance in gender inequality is more likely due to discrimination upstream to the editorial decision-making step. This would justify the continuation and expansion of institutional initiatives for mentorship and promotion of women's careers in sciences and unconscious bias training for editors as well as the importance of journals collecting and reporting on the gender of authors and peer reviewers.

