### 2.3.2. Aim and hypothesis

We postulate that acceptance rates for publication should differ by a factor 0.85 between women and men first authors among leading medical journals to confirm a gender bias. We aim to identify the influence of first-author gender on acceptance rates among original research articles sent for peer review by leading medical journals over an eight-year period.

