### **2.3.9. Statistical methods**

#### **2.3.9.1. Sample size**

As described above, we will consider an odds ratio of 0.85 for the acceptance for publication by first-author gender (0.85 for women versus men), to indicate the presence of gender bias. We assume a proportion of women first authors of 40% among cases and 44% among controls using  $OR=0.85$ . Taking into account a type-1 error at 5% (two-sided) with a study power of 90% and a correlation coefficient for exposure between matched controls and cases at 0.03 (to take into account some clustering at the journal level), this would require 2800 articles accepted and 2800 articles rejected after peer review. To take into account at least 20% of missing values among modelled variables, we will select a total of 3500 accepted and 3500 rejected manuscripts. We will randomly select an

equal number of articles per journal-year (20 cases and 20 controls) corresponding to a maximum of 160 cases and 160 controls for each journal. Currently, 23 journals have agreed to participate.

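### The 0.85 threshold is misworded in direction and put on two scales, and the conclusion from a null result does not require that a bias of 0.85 be excluded

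*Protocol*

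**What the plan says.** Protocol section 1.4 (Expected results and their impact) opens with "If we observe that the likelihood of acceptance is at least 0.85 (odds ratio) for women compared to men first authors". Such a result, it says, would help explain women's lower publication rates and slower academic advancement. It then turns to the opposite result: "If we do not find gender bias in editors' and reviewers' decision-making, we will be able to conclude that the imbalance in gender inequality". The rest of that sentence places the cause, as the more probable explanation, in discrimination before the editorial step. Section 1.4 adds that this would justify continuing and expanding institutional programmes.

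Section 2.3.2 (Aim and hypothesis) sets out the hypothesis on rates: "acceptance rates for publication should differ by a factor 0.85 between women and men first authors". Meeting this factor is what would confirm a bias. Section 1.3 (Methods) describes the outcome as a rate: "The primary outcome will be women's (or men's) rate of acceptance for publication after peer review".

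Section 2.3.9.1 (Sample size) states the effect as an odds ratio: "we will consider an odds ratio of 0.85 for the acceptance for publication by first-author gender". Women are compared with men, and this value is taken as the mark of bias. The section assumes 40% women among cases and 44% among controls, two-sided 5% and 90% power, and arrives at 2800 accepted and 2800 rejected articles. Section 2.3.9.2 analyses the odds of acceptance by mixed-effects logistic regression. Sections 2.3.8 and 2.3.9.1 fix equal numbers of cases and controls per journal-year.

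**The concern.** There are three separate problems, and all bear on how the main result will be read.

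- **Direction.** An OR of at least 0.85 is satisfied by no difference and by a difference in women's favour. Bias against women corresponds to low values.
- **Scale.** The same number is a ratio of rates in 2.3.2 and a ratio of odds in 1.4 and 2.3.9.1. These are different effects. A 1:1 sample of accepted and rejected papers estimates the OR directly. Its acceptance proportion is 50% by design, so it gives no acceptance rate without the sampling fractions or the cohort.
- **Null result.** Not finding bias is allowed to support a substantive conclusion about where discrimination lies. The protocol does not require the data to exclude the size of bias that it itself treats as relevant. A study that misses a real effect would support the same conclusion as one that rules it out.

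**Working it through.** **The plan's own effect size.** From 40% and 44%: (0.40/0.60)/(0.44/0.56) = 0.848. So 0.85 in 2.3.9.1 is an OR, for women versus men, in the direction of fewer acceptances for women. This settles the intended meaning.

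**Direction.** Inputs: n = 2800 per group; 44% women among controls; 40.04% among cases, which is the exact value for OR 0.85.

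SE(log OR) = √[1/(2800 × 0.4004 × 0.5996) + 1/(2800 × 0.44 × 0.56)] = 0.0542.

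With no bias, P(observed OR ≥ 0.85) = Φ(0.1625/0.0542) = Φ(3.00) ≈ 0.999. The pilot in section 2.2 (45% of women against 27% of men accepted) has OR (0.45/0.55)/(0.27/0.73) ≈ 2.2, and it too would meet the literal wording.

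**Scale.** The protocol gives no acceptance rate after peer review across journals, so men's rate is assumed to lie between 30% and 50%.

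| Men's acceptance (assumed) | Rate factor 0.85 as an OR | OR 0.85 as a rate ratio |
|---|---|---|
| 30% | (0.255/0.745)/(0.30/0.70) = 0.80 | 0.89 |
| 40% | (0.34/0.66)/(0.40/0.60) = 0.77 | 0.90 |
| 50% | (0.425/0.575)/(0.50/0.50) = 0.74 | 0.92 |

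The threshold in 2.3.2 is therefore a larger effect than the one the study is sized for.

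**Null result.** P(non-significant) ≈ 1 − Φ(|log OR|/0.0542 − 1.96).

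- True OR 0.85: 1 − Φ(1.04) = 0.15.
- True OR 0.90: 1 − Φ(−0.02) = 0.51.

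For example, an observed OR of 0.90 has a 95% CI of exp(−0.105 ± 0.106) = 0.81 to 1.00. It is just non-significant, and 0.85 lies inside it.

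The 15% is not the 10% implied by the stated 90% power, because 2800 per group does not reproduce at 90%. The usual two-sided formulas give about 3200 to 3370 per group, and 2800 gives about 84% to 86% power. That is a separate matter, and the present point does not depend on it. If 90% power did hold, the SE would be 0.1625/(1.96 + 1.28) = 0.0501, and the two figures would be 10% and 1 − Φ(0.1054/0.0501 − 1.96) ≈ 44%.

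**What an exclusion criterion would do.** With SE 0.0542, a 95% CI is wholly below 1 when log OR < −0.106. Its lower limit is above 0.85 when log OR > −0.056. Between these values the CI contains both 0.85 and 1.

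| True OR | CI wholly below 1 | CI contains 0.85 and 1 | Lower limit above 0.85 |
|---|---|---|---|
| 0.85 | 85% | 12% | 2.5% |
| 0.90 | 49% | 32% | 18% |
| 1.00 | 2.5% | 12% | 85% |

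At a true OR of 0.85, the chance of reaching the upstream conclusion falls from about 15% to 2.5%. With no bias, it is still reached in about 85% of studies.

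**The case against.** Section 1.4 is an impact narrative, and the operative text is 2.3.9.1 and 2.3.9.2, where direction, scale and model are clear. This stands, and it limits the point in four ways.

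- A reader might infer that the protocol would declare bias on a null result. It would not: 2.3.9.1 makes the intended direction plain, so the words in 1.4 are an error of expression.
- A reader might infer that 0.85 is a cut-off on the observed OR, which would be met only half the time when the true OR is 0.85. The text does not say so, and the two-sided sample-size calculation points to a significance test. The consequences of these different readings cannot be added together.
- A reader might infer that a null result is taken as proof. Section 1.4 says more likely, and section 2.5.2 is milder still, calling a null result useful information for others.
- A reader might infer that desk rejection is ignored because the case-control sample contains only peer-reviewed papers. Sections 1.2, 2.3.3, 2.3.7.1 and 2.3.9.2 cover the earlier decisions in the cohort, and 2.3.7.1 already plans acceptance rates by gender there. Those stage comparisons are, however, specified only as Chi-2 tests.

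It can also be said that a criterion for reading a null result belongs in a statistical analysis plan, which is not shown. But the protocol itself states what will be concluded from a null result, and that statement is too strong as written. The mismatch between 2.3.2 and 2.3.9.1 does not depend on any other document.

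**Conclusion.** The point holds as a should-fix. The wording in 1.4 contradicts the direction in 2.3.9.1. The threshold in 2.3.2 is on a different scale from the design and analysis, a gap of OR 0.85 against 0.80 to 0.74 for men's acceptance of 30% to 50%. The upstream conclusion can follow from a result that does not exclude the target bias: about 15% of studies at a true OR of 0.85 and 51% at 0.90, if not finding bias means a non-significant test.

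These figures use a crude standard error at 2800 complete articles per group. They ignore the 0.03 correlation, clustering by journal and covariates. The acceptance range is assumed. The choice of primary model and the validity of the case-control design are not affected.

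**What to change.** **Wording.** In 1.3, 1.4 and 2.3.2, express the primary effect and the threshold as an adjusted OR, women versus men. In 1.4, replace at least 0.85 with 0.85 or lower. Leave acceptance rates to the cohort, as 2.3.7.1 already plans.

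**Readings of the 95% CI for the adjusted OR, without overlap:**

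- wholly below 1: evidence of lower odds of acceptance for women, reported with whether 0.85 lies inside the interval;
- includes 1, with lower limit above 0.85: a bias as large as 0.85 is excluded;
- includes both 0.85 and 1: inconclusive;
- wholly above 1: no evidence of bias against women.

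**Upstream statement.** Allow it only when a bias of 0.85 is excluded and the CI is not wholly below 1. The second condition matters in the larger cohort, where an interval could lie wholly between 0.85 and 1. Limit the statement to decisions after peer review, unless the cohort's earlier-stage comparisons, reported as ORs with 95% CIs, meet the same criterion.

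**Cost.** Some results will be labelled inconclusive; with a true OR of 1 there is about an 85% chance of excluding 0.85. The cohort comparisons need a small amount of added analysis, since 2.3.9.2 plans only Chi-2 tests there. No new data are needed.
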